### Sample size and power considerations

2.13.

We estimated power based on means, standard deviations, and within-patient scale correlations over 6 months derived from our recent RCTs conducted with >500 patients as well as from the recent literature [37,38,46,53,61]. We originally planned to enroll 530 participants to randomize 400. However, due to a lower observed than estimated randomization rate in enrollment after study initiation (45.7%), we increased the target enrollment. We now estimate we will need to enroll ~875 patients to sufficiently safeguard against dropout before baseline and low post-discharge HADS scores at baseline to randomize 400. We conservatively assume 19% cumulative post-randomization dropout by 1 month, leaving 324, as well as an additional 15% dropout between 3 and 6 months [37,38,46]. Assuming a baseline standard deviation of 8.7 and correlation between baseline and 1 month of 0.4, this sample size will provide 90% power with an alpha of 0.05 to detect a treatment group difference of 2.6 units in the 3 month HADS total score, which represents an enduring effect difference similar to the minimal clinically important difference [62–64] in a comparison of two means via repeated-measures analysis. This will also provide 99% power with an alpha of 0.05 to detect a 2-unit difference in the primary outcome, the HADS total score at 1 month, as well as a 3.8-unit difference in the PTSS secondary outcome [61,65]. For subgroup analyses, in a comparison of two means in a repeated-measures analysis between baseline and 3 months, assuming a standard deviation of 4.5 and correlation between baseline and 3 months of 0.5, we will have 80% power with an alpha of 0.02 (to reasonably account for multiple comparisons) to detect group differences in the HADS total score of 4.2 units with a subgroup n of 100, 5.6 units with an n of 80, and 6.0 units with an n of 60, effects similar to those seen in the Blueprint 1 pilot RCT [38]. Power calculations were conducted via the comparison of two means in a repeated measures design in PASS (NCSS, Kaysville, UT).

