### Recruitment and eligibility

2.4.

Recruitment began October 15, 2024; as of manuscript publication date, recruitment is ongoing with a planned end date of October 15, 2027. Participants are being recruited from hospital ICUs affiliated with the following academic centers: Duke, OHSU, UCLA, and CU. Clinical research coordinators (CRCs) use local electronic medical records (EMRs) to screen patients in ICUs and stepdown units for potential eligibility and then approach for recruitment before hospital discharge. During the screening and consent process, the CRC provides an overview of the trial, shows a 2-min animated video created to explain the trial, and, if the patient is interested in participating, obtains their informed consent. We plan to consent 875 individuals to randomize 400 participants. Eligibility criteria, which is assessed in two stages (i.e., before and after discharge) can be found in Table 1.

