### Experimental condition allocation

2.5.

Within 48 h post-discharge, all enrolled participants are prompted by the mobile app to complete the HADS survey within the app. Patients with elevated HADS total scores (≥8) are stratified by language (English or Spanish) and auto-randomized within language group by the platform in a 1:1 group ratio using an adaptive, biased-coin minimization method to balance study site and the HADS total scale score < 20 vs. ≥20 in treatment group allocation [40]. This algorithm is programmed directly within the mobile app platform; details of the algorithm are in Appendix A of the Supplemental Material. After completing the baseline survey, the assigned Blueprint or Education Program content auto-populates the app platform and prompts program initiation.

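### With 324 analysed, the planned two-sided cLDA gives about 83–87% power for 2.6 HADS units at 3 months, not the stated 90%

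*Protocol article*

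**What the plan says.** The trial will randomize 400 participants 1:1 (Protocol article, sections 2.4 and 2.5). Section 2.13 then sets out attrition. For the first month it says: "We conservatively assume 19% cumulative post-randomization dropout by 1 month, leaving 324". For later follow-up it adds only a further 15% lost from month 3 to month 6. It gives no figure for months 1 to 3. The variance inputs follow: "Assuming a baseline standard deviation of 8.7 and correlation between baseline and 1 month of 0.4". The claim is that the number left "will provide 90% power with an alpha of 0.05 to detect a treatment group difference of 2.6 units in the 3 month HADS", and the effect is described as enduring and close to the minimal clinically important difference. The method is named as a comparison of two means in a repeated-measures design in PASS; the number of measurements and the sidedness are not given. For subgroups, the same section uses a baseline-to-3-month correlation of 0.5.

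Section 2.12 fixes the analysis: a cLDA with a common baseline intercept, separate group differences at each follow-up, and 95% confidence intervals. Section 2.10 makes HADS total at 1 month the primary outcome and HADS total at 3 months a secondary one.

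**The concern.** The 90% follows directly on the number left after dropout, so a reader takes it as the power the trial keeps once losses are counted. With the stated SD and correlation, the planned 3-month contrast reaches 90% at about the number randomized, not the number left. The inputs also belong to another visit: both the correlation and the remaining N are 1-month values. At stake is the statement about a lasting effect. If it is too favourable, a null 3-month result will be read as stronger evidence against durability than the design supports.

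**Working it through.** **Inputs (section 2.13 unless noted).** SD 8.7; correlation ρ = 0.4; difference 2.6; alpha 0.05; 400 randomized 1:1; 400 × 0.81 = 324 after 1-month dropout. The test is taken as two-sided because section 2.12 reports 95% intervals.

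**Formula for the planned contrast.** With a shared baseline mean, the group difference at a follow-up visit has SE = 2 × SD × √(1 − ρ²) / √N. Power = Φ(difference/SE − 1.960).

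**Where the stated 90% comes out**
- N = 400, ρ = 0.4: SE = 2 × 8.7 × √0.84 / 20 = 0.797; 2.6/0.797 = 3.261; power = Φ(1.301) = 90.3%.
- N needed for 90%: 4 × 8.7² × 0.84 × (1.960 + 1.282)² / 2.6² = 395.3, so 396 with equal arms.

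**After the plan's own dropout (N = 324)**
- ρ = 0.4: SE = 2 × 8.7 × √0.84 / 18 = 0.886; 2.6/0.886 = 2.935; power = Φ(0.975) = 83.5% (83.3% by noncentral t). Detectable at 90%: 3.242 × 0.886 = 2.87 units.
- ρ = 0.5: SE = 2 × 8.7 × √0.75 / 18 = 0.837; 2.6/0.837 = 3.106; power = Φ(1.146) = 87.4%. Detectable at 90%: 3.242 × 0.837 = 2.71 units.

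A full cLDA information calculation with 400 at baseline and 324 at months 1 and 3 gives the same 83.5% and 87.4%.

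**Routes that recover about 90% at 324 with ρ = 0.4**
- Mean of two repeated measures, factor (1 + ρ)/2 = 0.70: SE = 2 × 8.7 × √0.70 / 18 = 0.809; power = Φ(3.215 − 1.960) = 89.5%.
- One-sided 0.05 with factor 0.84: power = Φ(2.935 − 1.645) = 90.1%.

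The first tests an average over two occasions, not the 3-month difference. The second is not declared and does not go with 95% intervals.

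**Correlation that would restore 90% at 324.** 1 − ρ² = 0.84 × 324/395.3 = 0.688, so ρ is about 0.56. That is above both values in section 2.13.

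**Loss between months 1 and 3.** The document gives no figure, so these losses are assumptions. The cLDA calculation uses ρ = 0.4 with baseline and a 1-to-3-month correlation assumed between 0.4 and 0.8:
- 5% lost (N = 308): about 82–83%
- 10% lost (N = 292): about 80–82%
- 15% lost (N = 275): about 78–81%

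**The case against.** The best defence is that the 90% may have been computed on 324. Section 2.13 names a repeated-measures comparison of two means, and the averaged two-measure version of that method gives 89.5% there. A condensed article may leave the software settings to the full protocol. This stands in part: a reader might infer that the authors forgot to deduct dropout, or that 90% holds only if nearly all 400 are analysed, and the document does not establish either. It does not rescue the figure, because the claim is about the 3-month score and the averaged formula answers a different question. Nor can one say that baseline was entered as one of the two averaged measures, since the settings are not shown.

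It could also be said that the phrase about this sample size means 400. Then 90.3% reproduces, but the dropout allowance just stated plays no part in the claim.

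Two further readings go too far. One is that the chance of missing the effect is at least 1.6 times the implied 10%. It is 16.5% at ρ = 0.4, but 12.6%, about 1.3 times, at ρ = 0.5. The other is that power falls because the further 15% is lost by month 3. Section 2.13 places that loss after month 3, so N = 275 is only a scenario. The 0.5 is not settled either, since it comes from a subgroup calculation with a different SD (4.5).

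**Conclusion.** The figure is wrong as written, with moderate weight because the 3-month score is a secondary outcome. For the planned two-sided cLDA contrast with SD 8.7 and 324 observed at 3 months, power for 2.6 units is about 83% at correlation 0.4 and about 87% at 0.5. The difference detectable with 90% power is about 2.9 and 2.7 units respectively. The shortfall is therefore roughly 3 to 7 percentage points before any loss between months 1 and 3, and larger with such loss. This rests on two-sided testing, inferred from the 95% intervals, and on reading 324 as the analysed number. The true 3-month correlation is not given for the whole sample; a value of about 0.56 or more would remove the shortfall at 324.

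**What to change.** In section 2.13, restate the claim as about 83–87% power for a 2.6-unit difference at 3 months with 324 analysed, or 90% power for about 2.7–2.9 units. State that the test is two-sided, which N is used, and that the variance factor is 1 − ρ² to match the cLDA. Replace the baseline-to-1-month correlation with a named baseline-to-3-month value and its source, then narrow the range to that value. Add an assumed loss between months 1 and 3 and compute the 3-month power on what remains.

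This is a text correction. No patients are added and the analysis does not change; the stated power becomes slightly less favourable.

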### Statistical analysis

2.12.

Outcomes as well as patient characteristics will be characterized by group at baseline by mean (SD), median (IQR), and N (%), as appropriate. Analyses of primary and secondary outcomes will be performed utilizing constrained longitudinal data models (cLDA), which are mixed effects models where both groups are constrained to have the same baseline intercept. As recommended to improve precision [59,60], the model will be adjusted for randomization variables of site and primary language spoken. Random effects for subject and an unstructured covariance structure will account for correlation between repeated measures. Model estimates will include a shared baseline intercept, estimates for difference from baseline for 1–6 months, and estimates for difference between Blueprint and Education Control at 1–6 month timepoints. Estimates will be reported with a 95% CI and *p*-values will be used to determine significant differences.

In secondary subgroup analyses utilizing cLDA models as described above on subsets of participants, we will examine whether the intervention effects are consistent or vary in magnitude across pre-specified sociodemographic subgroups that might have comparatively less access to therapy on average: Black race, Hispanic ethnicity, and participants with Spanish as a primary language (i.e., participants using the Spanish-language version of the app). Sensitivity analyses will be performed to estimate how much loss to follow-up may have affected primary outcome effect estimates using cLDA models with 1-month values imputed from linear regressions of any available weekly HADS scores collected during the intervention.

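### The stated 99% power for a 2-unit difference in the primary outcome does not follow from section 2.13's own inputs, which give about 61% to 69%

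*Protocol article*

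**What the plan says.** All the figures stand in one paragraph of the protocol article, section 2.13 (Sample size and power considerations).

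- Retained sample: "We conservatively assume 19% cumulative post-randomization dropout by 1 month, leaving 324". The next stated loss falls between 3 and 6 months, so 324 applies at both 1 and 3 months.
- Variability: "Assuming a baseline standard deviation of 8.7 and correlation between baseline and 1 month of 0.4".
- Claim at 3 months: "90% power with an alpha of 0.05 to detect a treatment group difference of 2.6 units in the 3 month HADS total score".
- Claim for the primary outcome, in the following sentence: "This will also provide 99% power with an alpha of 0.05 to detect a 2-unit difference in the primary outcome". That sentence also covers a 3.8-unit difference in the PTSS.
- Subgroups, again for HADS total: "assuming a standard deviation of 4.5 and correlation between baseline and 3 months of 0.5".

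The power method is named as a comparison of two means in a repeated-measures design in PASS. Section 2.12 plans a constrained longitudinal (cLDA) model with a shared baseline intercept.

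**The concern.** With sample, alpha and variance held fixed, power falls as the target difference shrinks. Here it rises from 90% to 99% while the difference drops from 2.6 to 2 units on the same scale. That is possible only if the 1-month contrast has a much smaller variance than the 3-month one, and the section states no such variance.

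This is the article's only power statement for the primary endpoint. A reader, the DSMB or the funder would take from it that a true 2-unit benefit is almost certain to be detected.

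**Working it through.** **Inputs.** All are from section 2.13 unless noted.
- SD 8.7; correlation r = 0.4.
- 324 retained (400 × 0.81). Allocation is 1:1 (section 2.5), so 162 per arm.
- Alpha 0.05. Sidedness is not stated. Two-sided is assumed, in line with section 2.12: "Estimates will be reported with a 95% CI".

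**Formulas.** Standard error of the group difference: SE = s × √(2/162) = s / 9, where s is the effective SD:
- cLDA (baseline-adjusted, close to ANCOVA): s = 8.7 × √(1 − 0.4²) = 7.97, SE = 0.886
- average of two repeated measures: s = 8.7 × √((1 + 0.4)/2) = 7.28, SE = 0.809
- follow-up score only: s = 8.7, SE = 0.967
- change score: s = 8.7 × √(2 × (1 − 0.4)) = 9.53, SE = 1.059

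**Step 1: reproduce the companion figure (90% for 2.6 units).** The two-measure average gives 89.3% (noncentral t), and its 90% detectable difference is (1.960 + 1.282) × 0.809 = 2.62 units. That matches. The cLDA variance gives 83.3% at 162 per arm. It reaches 90.3% (normal approximation) only with 200 per arm, that is, without dropout.

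**Step 2: apply the same inputs to 2 units.** Noncentral t, 162 per arm:

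| Variance | Power, 2 units | Power, 2.6 units |
|---|---|---|
| cLDA | 61.4% | 83.3% |
| Two-measure average | 69.3% | 89.3% |
| Follow-up only | 54.1% | 76.5% |
| Change score | 46.9% | 68.7% |

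Check by normal approximation: cLDA 2/0.886 = 2.26, and Φ(2.26 − 1.96) ≈ 0.62; two-measure 2/0.809 = 2.47, and Φ(2.47 − 1.96) ≈ 0.70.

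**Step 3: try more generous settings.**
- One-sided alpha 0.05: 73% (cLDA) or 80% (two-measure average).
- No dropout, 200 per arm, two-sided: 71% or 78%.
- Averaging 3 to 8 equally correlated measures at 162 per arm: 76% to 85%.
- Baseline-adjusted average of three follow-ups at 162 per arm: 88%, or 93% one-sided.

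None reaches 99%, and the averages are not the 1-month endpoint.

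**Step 4: what 99% would need.** At 162 per arm the effective SD must be 2 × 9 / (1.960 + 2.326) = 4.20. The raw SD at r = 0.4 is then 4.20/0.917 = 4.6 under cLDA, or 4.20/0.837 = 5.0 under the two-measure average. Keeping SD 8.7 under cLDA would need r of about 0.88.

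**Step 5: differences detectable at 162 per arm.**

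| Power | cLDA | Two-measure average |
|---|---|---|
| 80% | 2.5 | 2.3 |
| 90% | 2.9 | 2.6 |
| 99% | 3.8 | 3.5 |

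**The case against.** **The inputs may not carry over.** The SD and correlation are attached grammatically to the 3-month calculation, and the sentence with the 99% also covers the PTSS, which must have its own, unstated SD. This is fair as far as it goes: the text does not say outright that 8.7 underlies the 99%. But the correlation is labelled baseline to 1 month, which is the primary timepoint, and the wording presents the 99% as a further property of the same sample size. If other inputs were used, they are unstated and imply a much smaller SD or a much higher correlation for the same scale. The paragraph needs correction either way.

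**No single figure is the right one.** This stands. The 61% fits the planned analysis, while the 69% comes from the formula that reproduces the 2.6-unit claim and is closer to the stated power method. Both belong in the statement; neither is near 99%.

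**A reader might infer that the subgroup SD of 4.5 was used by mistake.** With SD 4.5 and r = 0.4 the cLDA variance does give 99.2%. The documents do not support going further:
- The text never links 4.5 to the 99%.
- SD 4.5 does not reproduce the results it is printed for. With alpha 0.02, 80% power, r = 0.5 and n = 100 (50 per arm), baseline adjustment gives (2.326 + 0.842) × 4.5 × √0.75 × √(2/50) = 2.5 units, and follow-up only gives 2.9, against 4.2 stated. SD 8.7 with baseline adjustment gives 4.8, 5.3 and 6.2 for n = 100, 80 and 60, nearer to the stated 4.2, 5.6 and 6.0. So 4.5 may itself be the misprint.
- There are other routes to a similar figure. Averaging seven or eight HADS measures with first-order autoregressive correlation 0.4 and SD 8.7 gives 97% or 98% at 162 per arm. Such an average is not the 1-month endpoint, so it does not rescue the claim.

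**A reader might also infer that a null result would be taken to exclude a 2-unit benefit.** That is too strong. Section 2.12 commits to reporting estimates with 95% confidence intervals, which show whether 2 units is excluded whatever the planned power was.

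**Conclusion.** The 99% is wrong as written. On the only full-sample inputs in section 2.13, power for 2 units at 1 month is about 61% under the planned cLDA variance and about 69% under the two-measure formula that reproduces the 2.6-unit claim. Other standard single-contrast formulas give less (47% to 54%). The 99% and 90% statements also cannot both hold without a different variance that the section does not give.

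This rests on two-sided alpha 0.05, 162 analysed per arm, and SD 8.7 with r = 0.4 applying at 1 month. The source of the 99% cannot be determined from the text. The error touches the stated justification of the sample size; it changes no randomised number, endpoint or analysis.

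**What to change.** Rerun every full-sample power figure in section 2.13 under one named method and restate them together, so that the 1-month and 3-month HADS statements agree. On SD 8.7, r = 0.4, 324 analysed and two-sided alpha 0.05, state either:

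- **cLDA variance:** about 61% power for 2 units and 83% for 2.6; detectable differences 2.5 units (80%), 2.9 (90%) and 3.8 (99%); or
- **two-measure average:** about 69% for 2 units and 89% for 2.6; detectable differences 2.3 units (80%), 2.6 (90%) and 3.5 (99%).

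Correcting only the 1-month figure on the cLDA basis would leave 90% for 2.9 units at 1 month beside 90% for 2.6 units at 3 months on identical inputs, which is a new contradiction.

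If the 99% came from other inputs, state the SD and correlation with their source. In either case, reconcile the 8.7 and 4.5 given for HADS total, and state the sidedness of the test.

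Cost: a rerun of the power calculation and a text correction. No extra patients are needed. The stated power for the primary endpoint becomes less favourable.

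### The subgroup detectable differences of 4.2, 5.6 and 6.0 HADS units do not follow from the stated SD and correlation, and no single set of inputs gives all three

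*Protocol article*

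**What the plan says.** All of this stands in the protocol article, section 2.13 (Sample size and power considerations).

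- **Main calculation for HADS total:** "Assuming a baseline standard deviation of 8.7 and correlation between baseline and 1 month of 0.4", with 324 participants left at 1 month, giving "90% power with an alpha of 0.05 to detect a treatment group difference of 2.6 units in the 3 month HADS total score".
- **Subgroup calculation for the same scale:** a comparison of two means in a repeated-measures analysis from baseline to 3 months, "assuming a standard deviation of 4.5 and correlation between baseline and 3 months of 0.5", at 80% power and alpha 0.02.
- **Result given for subgroups:** "4.2 units with a subgroup n of 100, 5.6 units with an n of 80, and 6.0 units with an n of 60".

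Section 2.12 names the subgroups (Black race, Hispanic ethnicity, Spanish as primary language) and calls these analyses secondary. Section 2.2 makes differential response among sociodemographic subgroups part of the study aims.

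**The concern.** Three things look wrong on reading the sentence.

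1. An SD of 4.5 seems too small to need differences as large as 4.2 to 6.0 units at these sample sizes.
2. The step from n=100 to n=80 raises the difference by a third, while the step from 80 to 60 raises it by only 7%. The second is the larger proportional cut in n, so this is the wrong way round.
3. The SD is roughly half the one used earlier in the same section for the same scale.

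This sentence is the article's only statement of what the subgroup analyses can detect. As it stands, a reader cannot tell whether a subgroup of 100 can reliably show a difference of about 2.5 units or of about 5. That matters when a null or imprecise result, for instance among Spanish-language users, has to be interpreted.

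**Working it through.** **Inputs (section 2.13 unless noted).** SD 4.5; correlation ρ = 0.5; alpha 0.02, taken as two-sided; power 80%; subgroup totals 100, 80 and 60; 1:1 allocation (section 2.5). For comparison: SD 8.7, ρ = 0.4, alpha 0.05, n = 324, difference 2.6.

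**Formula.** With a total of n split equally,

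SE = SD × f × √(4/n), and detectable difference = SE × (z for alpha + z for power).

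The factor f depends on the variance form, which the article does not name:

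- ANCOVA form, close to the constrained longitudinal model of section 2.12: f = √(1 − ρ²)
- mean of two repeated measures: f = √((1 + ρ)/2)
- change score: f = √(2(1 − ρ))
- follow-up score alone: f = 1

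At ρ = 0.5 the first two both equal √0.75 = 0.866 and the last two both equal 1, so there are only two cases to carry.

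**Step 1: the plan's main figure.** Mean of two measures, ρ = 0.4: SE = 8.7 × √0.7 × √(4/324) = 0.809. Then 2.6/0.809 = 3.21, and 3.21 − 1.96 = 1.25, giving power of 89.5%. This reproduces the stated 90%, so the same kind of formula should reproduce the subgroup figures.

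**Step 2: the subgroup figures from the stated inputs.** The multiplier is 2.326 + 0.842 = 3.168. For n=100 with f = 0.866: 4.5 × 0.866 × 0.2 × 3.168 = 2.47. Ranges below run from the normal approximation to noncentral t.

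| n | Stated | f = 0.866 | f = 1 | Power at the stated difference, f = 1 (normal) |
|---|---|---|---|---|
| 100 | 4.2 | 2.47–2.50 | 2.85–2.89 | 99.0% |
| 80 | 5.6 | 2.76–2.81 | 3.19–3.24 | 99.9% |
| 60 | 6.0 | 3.19–3.27 | 3.68–3.77 | 99.8% |

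With f = 0.866 power is higher still. Other readings do not close the gap. One-sided alpha, or n read as per arm, makes the differences smaller. Cutting n by 19% and then 15% with f = 1 gives 3.44, 3.84 and 4.44, the largest values found at SD 4.5. A treatment-by-subgroup contrast against the rest of the sample also stays below the printed values.

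**Step 3: consistency among the three figures.** With SD, correlation, alpha and power fixed, difference × √n should be constant:

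- 4.2 × √100 = 42.0 (41.5–42.5 allowing for rounding of the difference)
- 5.6 × √80 = 50.1 (49.6–50.5)
- 6.0 × √60 = 46.5 (46.1–46.9)

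The ranges do not overlap. Any constant variance factor or dropout fraction cancels here, so this check does not depend on the formula, and the small-sample t correction is far too small to explain it. Scaling from 4.2 at n=100 gives 4.2 × √(100/80) = 4.70 and 4.2 × √(100/60) = 5.42. Solving for the SD by noncentral t gives about 7.6, 9.0 and 8.3 (f = 0.866) or 6.5, 7.8 and 7.2 (f = 1).

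**Step 4: if the SD were 8.7 (assumption, ρ kept at 0.5).** 4.5/8.7 = 0.52. Ranges cover both variance forms and both approximations.

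| n | Stated | Detectable difference | Power at the stated difference |
|---|---|---|---|
| 100 | 4.2 | 4.8–5.6 | 52–68% |
| 80 | 5.6 | 5.3–6.3 | 69–84% |
| 60 | 6.0 | 6.2–7.3 | 61–78% |

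So 8.7 does not give all three figures either.

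**The case against.** The arithmetic is hard to contest: the sentence is complete, its inputs are all printed, and no reading tried recovers the figures. The case on the other side is about how much to make of it, and most of that stands.

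- **A reader might infer that 4.5 is simply the wrong SD and that subgroup power is therefore overstated.** The article does not support that. It labels 8.7 a baseline SD and leaves 4.5 unlabelled, so they may be different quantities, and the earlier trials behind them are not at hand. If 4.5 is right, the printed differences err on the cautious side. Overstatement follows only if 8.7 applies, and then it is clearest at n=100. At n=80 the stated 5.6 lies inside the recomputed range.
- **A reader might take one recomputed row as the correct replacement.** The article does not name the variance form, and the form moves the answer by about 15% (1/0.866). The ranges above show the size of the problem; they are not values to paste in.
- **A reader might think the trial's size is in doubt.** It is not. The 400 to be randomized and the roughly 875 to be enrolled do not depend on the subgroup figures, and 100, 80 and 60 are not tied to any recruitment target.
- **The figures do rise as n falls.** That is true. The fault is that they do not follow 1/√n.

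What the objection does not remove is that the printed inputs and outputs contradict each other, for analyses that serve a stated aim.

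**Conclusion.** The point holds in this form. The stated inputs give detectable differences of about 2.5–2.9, 2.8–3.2 and 3.2–3.8 units, so the printed 4.2, 5.6 and 6.0 are roughly 1.5 to 2 times too large for them. The three values also cannot all come from one SD, correlation and dropout fraction. The mutual inconsistency depends on no choice of formula. The size of the mismatch assumes 1:1 allocation, two-sided alpha and n as the subgroup total; the alternatives tried do not remove it.

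The direction of the error cannot be settled from the article: cautious if 4.5 is right, optimistic at n=100 if 8.7 is. The gap between the two SDs is an unexplained discrepancy, not a proven mistake. This is a should-fix correction to the stated sensitivity of secondary subgroup analyses, with no effect on the primary sample size.

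**What to change.** In section 2.13:

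1. Say what the 4.5 is (which measure, which time point, which source) and reconcile it with the 8.7, or correct whichever is wrong.
2. Re-run the three subgroup cases from one justified SD, one correlation and one named variance form.
3. Replace the three printed differences with the results, and check that they scale with 1/√n.
4. Check that the closing remark likening these effects to those of the pilot trial still holds for the new values.

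The cost is a short re-run in the software already used and a text correction. Nothing changes in recruitment, data collection or the planned models. Recruitment is ongoing, with a planned end in October 2027, so the correction can be made before any subgroup result is read against these figures.
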